### Randomization and Blinding

Eligible participants will be randomly allocated (1:1 ratio) into either the Intervention (VR) or Control group. To ensure proper allocation concealment, a computer-generated randomization sequence will be created by an independent researcher not involved in clinical care or data collection. The allocation sequence will be concealed using sequentially numbered, opaque, sealed envelopes, which will only be opened after the patient has consented to participate. Due to the nature of the VR intervention, blinding of patients and the administering clinician is not possible. However, the study will use an assessor-blinded approach; laboratory personnel analyzing the salivary biomarkers, and statisticians conducting the data analysis will be strictly blinded to group assignments.

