### Outcomes and Data Collection

Data collection occurs at three standardized time points: Baseline (immediately before the VR or verbal education intervention), Post-test 1 (immediately after the intervention), and Post-test 2 (15 minutes after the intervention). The subjective anxiety assessment uses the APAIS, comprising 6 items scored on a 5-point Likert scale, with total scores ranging from 6 to 30, categorized from “Not Anxious” to “Panic.” Objective physiological assessments include blood pressure (systolic/diastolic), heart rate, and respiratory rate, which will be measured after the patient has rested for at least 5‐10 minutes.

For objective biochemical assessments, unstimulated saliva samples (4‐5 mL) will be collected via the spitting method at the three designated time points. To ensure optimal long-term preservation of the stress biomarkers prior to enzyme-linked immunosorbent assay (ELISA) analysis, samples will be initially frozen at −10 °C and subsequently transferred to a −80 °C freezer. Salivary Alpha-Amylase (sAA) will be analyzed to measure sympathetic nervous system activity, while Salivary Cortisol will be measured to assess HPA axis activity.

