### Sample Size

The sample size was calculated using the formula for unpaired analytical studies with numerical data. Based on a 95% confidence level (Zα=1.96) and 80% power (Zβ=0.84), the minimum sample size is 16 participants per group, totaling 32 participants.

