### Statistical Analysis

Data will be analyzed using SPSS version 25.0 (IBM Corp). Descriptive statistics will be used to summarize the demographic and clinical characteristics of the participants. The Shapiro-Wilk test will be utilized to assess the normality of the data distribution, given the sample size is less than 50. Because this study involves repeated measurements across three time points, repeated-measures Analysis of Variance (ANOVA) will be conducted for normally distributed data to evaluate the main effects of time, group assignment, and the time-by-group interaction. If the data violate the assumption of normality, non-parametric alternatives such as Generalized Estimating Equations (GEE) or the Friedman test will be applied. To comprehensively report the magnitude of the intervention’s effect, effect sizes (eg, partial eta-squared or Cohen *d*) and 95% confidence intervals will be presented alongside the *P* values. A *P* value of <.05 is considered statistically significant..

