## Results

The study is currently in the preparation phase. Data collection is scheduled to take place from May 2026 to July 2026. The analysis will focus on the differences in APAIS scores, sAA levels, cortisol levels, and vital signs between the two groups.

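### The Friedman test is named as a fallback for the two-group repeated-measures ANOVA, but it has no group term and cannot compare VR with control

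*Protocol article*

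**What the plan says.** The design has two randomised arms: "Eligible participants will be randomly allocated (1:1 ratio) into either the Intervention (VR) or Control group". Outcomes are measured repeatedly: "Data collection occurs at three standardized time points" (baseline, immediately after the session, and 15 minutes after it).

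The target is a comparison of arms. The Results section states: "The analysis will focus on the differences in APAIS scores, sAA levels, cortisol levels, and vital signs between the two groups". The hypothesis under Principal Findings is also VR against verbal education, and the sample size was "calculated using the formula for unpaired analytical studies with numerical data", which is a formula for two independent groups.

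Under Statistical Analysis, "The Shapiro-Wilk test will be utilized to assess the normality of the data distribution". Outcomes judged normal go to repeated-measures ANOVA, with main effects of time and group and their interaction. For the rest, "alternatives such as Generalized Estimating Equations (GEE) or the Friedman test will be applied", and both methods are described there as non-parametric. The section does not say which of the two is used when, or how the arms would be compared under Friedman.

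The Methods paragraph of the Abstract lists another set: independent and paired t tests, or Mann-Whitney and Wilcoxon tests, depending on normality.

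**The concern.** A fallback should answer the same question as the analysis it replaces. The ANOVA branch tests group and time-by-group effects. Friedman is a one-sample test of whether the time points differ, so both of those effects disappear once it is chosen.

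The rule covers every outcome that fails the normality check, so APAIS and the vital signs are affected as well as salivary alpha-amylase and cortisol. Two things would follow for such an outcome. A change over time common to both arms could be reported as a positive result, and a real difference between arms could go undetected. A common change is plausible, because both arms receive a 10-minute information session and are then measured again, and cortisol is sampled in a morning window chosen for its circadian rhythm.

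**Working it through.** **1. The plan's own figure.** "the minimum sample size is 16 participants per group, totaling 32 participants", from Z values of 1.96 and 0.84. For two independent means, n per group = 2(1.96 + 0.84)² / d² = 15.68 / d². The article gives neither a mean difference nor an SD, so 16 cannot be reproduced, only inverted: d = √(15.68/16) = 0.99, up to √(15.68/15) = 1.02 before n rounds up to 16. Nothing below depends on d. The formula does confirm that the trial was sized for a between-group comparison.

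**2. What Friedman computes.** With n participants, k = 3 time points and rank sums R₁, R₂, R₃:

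Q = 12 / [n k (k+1)] × ΣRⱼ² − 3n(k+1)

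For n = 32 this is Q = ΣRⱼ² / 32 − 384, on 2 degrees of freedom. Group does not appear, so moving any participant from VR to control leaves Q unchanged. Two extreme cases show the effect:

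- *Largest possible difference between arms.* All 16 VR participants fall steadily (ranks 3, 2, 1) and all 16 controls rise steadily (ranks 1, 2, 3). Each rank sum is 64. Q = 3 × 4096/32 − 384 = 0, so P = 1.
- *No difference between arms.* All 32 fall steadily. Rank sums are 96, 64 and 32. Q = (9216 + 4096 + 1024)/32 − 384 = 448 − 384 = 64, so P is far below .05.

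**3. Size in realistic settings.** Assumptions that are not in the article: log-normal outcomes, 16 per arm, three time points, shifts in SD units on the log scale. The comparator is a between-arm Mann-Whitney test on the log change from baseline to 15 minutes.

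| Setting | Pooled Friedman P<.05 | Between-arm test P<.05 |
|---|---|---|
| No VR effect; same linear fall of 0.3–0.5 SD in both arms; correlation 0.5–0.7 | roughly 23–78% | about 5% |
| No VR effect; same fall of 0.6 SD at both post-tests; correlation 0.6 | 91% | 4.8% |
| Arms move +0.4 and −0.4 SD; correlation 0.6 | about 4% | about 65% |

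A repeat of the first row with 4,000 trials per setting gave 20% to 78%, so its lower end is good only to a few points. The range also depends on the shape of the fall: when step falls are included, it widens to about 22–88%.

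**4. GEE.** A GEE with group, time and group-by-time terms tests the same contrast as the ANOVA. It specifies a mean model and a working correlation, so it is a semi-parametric marginal model. In 400 simulated trials with no VR effect, the interaction test rejected in about 7.8% with the ordinary robust variance and about 4.8% with a bias-reduced variance (Monte Carlo error about 1 point). The article does not say which variance would be used.

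**The case against.** The strongest reply is that the first fallback named, GEE, does test VR against control, that the wording makes the list illustrative, and that a separate analysis plan may settle the choice. The first part stands and limits the severity. The last does not remove the point. An analysis plan can choose among valid options, but here the article itself names a test that cannot do the job it is given.

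A second reply is that the Abstract names Mann-Whitney, a two-group test, for non-normal data. That is true, so the article as a whole is not without one. Statistical Analysis does not carry it over, however, and the two lists disagree. This is a further reason to reconcile them.

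A reader might infer three stronger criticisms, which the document does not support:

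- *That GEE is also the wrong test, or has an inflated error rate.* Its label is wrong, but its contrast is right. The rate of about 8% assumes an uncorrected variance that the article never specifies.
- *That the trial will run Friedman in each arm and contrast the two P values.* That would be invalid, but no section plans it, and the stated target is the difference between groups.
- *That the normality check and the ANOVA must go.* There are arguments for other models, but this error does not require redesigning the branch for normal data.

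**Conclusion.** The point holds for the Friedman test. As a substitute for the two-group ANOVA it leaves the trial's question untested for any outcome sent to it, and its P value is not evidence for or against VR. That follows from the form of the statistic and needs no assumptions. The percentages do rest on assumptions (16 per arm, the stated correlations, and the size and shape of the change). They show the direction and rough scale, and do not predict this trial's error rates.

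The fault is in what is stated: the option offered is wrong for its purpose. It should be fixed, but it is not fatal, because GEE can supply the comparison if it is chosen and fitted with the group and interaction terms.

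**What to change.** In Statistical Analysis, delete the Friedman test as a fallback for the comparison of arms and name, before data are collected, one fallback that contains the group contrast. Any of these would serve:

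- GEE with group, time and group-by-time terms and a small-sample-corrected variance.
- A baseline-adjusted model on log-transformed alpha-amylase and cortisol. The downside is that effects are then reported as ratios.
- A rank-based between-arm test of change from baseline, with the time point named in advance.

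The chosen fallback should be defined for APAIS and vital signs as well as for the biomarkers. Describe GEE as a semi-parametric marginal model. Bring the Abstract's list of t, Mann-Whitney and Wilcoxon tests into line with the section.

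The cost is a few sentences of text. No new data, visits or participants are needed, and the Results section describes the study as still in preparation.

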### Ethical Considerations

This study has been approved by the Research Ethics Committee of Universitas Padjadjaran (approval #344/UN6.KEP/EC/2026). Written informed consent will be obtained from all participants prior to enrollment, in strict adherence to the principles outlined in the Declaration of Helsinki.

## Results

The study is currently in the preparation phase. Data collection is scheduled to take place from May 2026 to July 2026. The analysis will focus on the differences in APAIS scores, sAA levels, cortisol levels, and vital signs between the two groups.

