## Discussion

### Principal Findings

This protocol outlines a randomized controlled trial designed to evaluate the efficacy of immersive Virtual reality (VR) as a nonpharmacological anxiolytic intervention for adult patients undergoing odontectomy under general anesthesia. We hypothesize that the preoperative VR intervention will significantly mitigate anxiety compared to standard verbal education [10]. Specifically, we anticipate that patients exposed to the 360 degree virtual operating room environment will exhibit lower subjective anxiety scores on the APAIS, more stable physiological parameters (blood pressure, heart rate, and respiratory rate), and significantly reduced levels of stress-related salivary biomarkers, namely cortisol and alpha-amylase [10,11].

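### Seven anxiety outcomes are tested at P<.05 with no primary outcome, time point or contrast, so the 5% level does not describe the error rate of the efficacy conclusion

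*Protocol article*

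**What the plan says.** Outcomes and Data Collection lists seven outcomes:

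- One self-report scale: "The subjective anxiety assessment uses the APAIS, comprising 6 items scored on a 5-point Likert scale", with a total of 6 to 30.
- Four vital signs: "Objective physiological assessments include blood pressure (systolic/diastolic), heart rate, and respiratory rate".
- Two salivary markers: "Salivary Alpha-Amylase (sAA) will be analyzed to measure sympathetic nervous system activity, while Salivary Cortisol will be measured to assess HPA axis activity".

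Each is taken at baseline, immediately after the session, and 15 minutes later. None is called primary there or anywhere else.

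Sample Size gives the error rates and the total but no endpoint, standard deviation or difference: "Based on a 95% confidence level (Zα=1.96) and 80% power (Zβ=0.84), the minimum sample size is 16 participants per group, totaling 32 participants".

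Statistical Analysis plans a repeated-measures ANOVA per outcome, with time, group and time-by-group effects, or a non-parametric alternative. The Abstract plans independent and paired t tests or their rank-based counterparts. Statistical Analysis sets a single threshold, a P "value of <.05 is considered statistically significant", and mentions no adjustment.

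The Results section says: "The analysis will focus on the differences in APAIS scores, sAA levels, cortisol levels, and vital signs between the two groups". Principal Findings gathers all the outcomes under one hypothesis, expecting that VR patients "will exhibit lower subjective anxiety scores on the APAIS, more stable physiological parameters (blood pressure, heart rate, and respiratory rate), and significantly reduced levels" of the salivary biomarkers.

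**The concern.** The trial asks one question, whether VR reduces preoperative anxiety, and offers seven answers of equal rank. Nothing says which answer decides, at which post-test time, or from which term of the model. A mixed result is foreseeable. APAIS is self-reported by patients who know their group, whereas the salivary assays are run by blinded laboratory staff, and Strengths and Limitations concedes that novelty and expectancy may alter the anxiety response. If APAIS improves and cortisol does not, or the reverse, the protocol does not say whether VR worked.

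The choice would then be made after the data are seen, and the nominal 5% would no longer describe the risk of a false efficacy conclusion. Implications and Future Directions foresees a change in preoperative care if the hypothesis is borne out, so the rule for deciding that matters.

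**Working it through.** **Inputs from the protocol.** Outcomes: 1 (APAIS) + 4 (vital signs) + 2 (salivary markers) = 7. Post-test times: 2. Threshold per test: 0.05. Sample size: 16 per group, with Z values 1.96 and 0.84.

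**Assumed inputs.** The document gives no correlations. I take the between-outcome correlation from 0 to 0.7 and the between-time correlation as 0.7.

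**1. The plan's own figure.** The usual formula is n = 2 × ((1.96 + 0.84)/d)², where d is the difference in SD units. With no endpoint, SD or difference stated, 16 cannot be reproduced, only inverted: d = 2.80 × √(2/16) = 0.99. The document does not say on which outcome a difference of about 1 SD is expected.

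**2. Independent tests, as a ceiling.** For 7 tests, 1 − 0.95⁷ = 0.302. For 14 tests (7 outcomes × 2 times), 1 − 0.95¹⁴ = 0.512. The second figure is not realistic: systolic and diastolic pressure, or one measure taken twice within 15 minutes, will be correlated.

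**3. Correlated tests.** Simulation with no VR effect, 16 per arm and normal data; entries are the chance of at least one P<.05. Ranges reflect simulation settings and Monte Carlo variation.

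| What may count as support | Outcome correlation 0 | 0.3 | 0.5 | 0.7 |
|---|---|---|---|---|
| Time-by-group interaction, one per outcome (7 tests) | 30% | 28% | 24% | 18–19% |
| Group effect or interaction, per outcome | 50–52% | 47–48% | 41–42% | 33% |
| t tests at both post-test times (14 tests), either direction | 45–47% | 42% | 36–37% | 28–30% |
| The same 14 t tests, favouring VR only | 26% | 21–22% | 18–19% | 14–15% |

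The first two rows follow the ANOVA in Statistical Analysis; the last two follow the Abstract. For comparison, one pre-specified two-sided test gives 5% in either direction and 2.5% favouring VR.

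**4. The opposite rule, all outcomes must agree.** The false-positive risk then cannot exceed 5%, but power falls. With d = 0.99 and 16 per arm, a t test on one outcome has 77% power. If all seven outcomes truly had that effect and were independent, joint power would be 0.77⁷ = 0.16. Correlation would raise this figure.

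**The case against.** The strongest reply is that no passage lets a single significant result carry the efficacy claim. Principal Findings joins its expectations with a conjunction: lower APAIS scores, steadier vital signs and lower biomarkers. Read as a requirement that all agree, the error rate does not inflate. This stands as far as it goes. A reader might infer that any one of 14 comparisons suffices and that the true error rate is about 50%, but the document does not say so. Nor does it say that all must agree; that passage describes what is anticipated, not how success is judged. The defect is that the rule is unstated, and the percentages hold only under the lenient reading.

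Three further points narrow the size:

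- The 14-test count follows the Abstract. The Methods fit one model per outcome with time inside it, which is the lower 18–30% range if only the interaction counts. Statistical Analysis does not say whether the group effect or the interaction decides, so the 33–50% range remains open.
- The either-direction figures include results in which VR looks worse, and these cannot support efficacy. The directional risk is about half as large.
- The independence figure of 51% should not be used as an estimate.

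It may also be said that multiplicity procedures and the reading of discordant results belong in an analysis plan that is not shown. That is fair for the adjustment method. It does not cover the primary outcome: the article has its own outcomes, sample-size and analysis sections, and a sample size is calculated for a particular outcome. Here the outcomes are listed as equals in each place where a hierarchy would appear.

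**Conclusion.** The point holds in this form: seven outcomes at two post-test times bear on one claim, each judged at P<.05, with no primary outcome, time point or contrast and a sample size tied to none of them. The trial therefore has no defined positive or negative result.

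If any significant outcome may be read as support, the false-positive chance is several times the nominal level under every analysis the document describes, even with outcomes correlated at 0.7. The lowest either-direction figure examined there, 18%, is more than three times 5%. The lowest directional figure for the 14 t tests, about 14–15%, is more than five times 2.5%. These sizes depend on assumed correlations and on the lenient reading. Under the strict reading the problem becomes lost power instead. The document supports neither reading over the other, and this should be settled before any data are seen.

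**What to change.** Before enrolment, name one primary outcome, one time point and one contrast. An example is the between-group difference in the APAIS total score (the 6–30 total the protocol defines) at one stated post-test time, adjusted for baseline, two-sided 0.05. The single corresponding contrast from the planned repeated-measures model would serve equally well and stays closer to Statistical Analysis. The choice between the two post-test times is the sponsor's; what matters is that one is fixed in advance. Sample Size should then state that it refers to this comparison.

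Make alpha-amylase, cortisol and the four vital signs secondary, either with Holm adjustment or reported as estimates with 95% confidence intervals labelled supportive. State that efficacy is claimed only on the primary comparison. That returns the error rate of the efficacy claim to 5%.

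The cost is about one paragraph, and the Results section describes the study as still in preparation. The sponsor gives up claiming efficacy from an isolated secondary result.

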## Discussion

### Principal Findings

This protocol outlines a randomized controlled trial designed to evaluate the efficacy of immersive Virtual reality (VR) as a nonpharmacological anxiolytic intervention for adult patients undergoing odontectomy under general anesthesia. We hypothesize that the preoperative VR intervention will significantly mitigate anxiety compared to standard verbal education [10]. Specifically, we anticipate that patients exposed to the 360 degree virtual operating room environment will exhibit lower subjective anxiety scores on the APAIS, more stable physiological parameters (blood pressure, heart rate, and respiratory rate), and significantly reduced levels of stress-related salivary biomarkers, namely cortisol and alpha-amylase [10,11].

### Comparison to Prior Work

Previous research has consistently demonstrated the use of VR in reducing anxiety during various medical and dental procedures [9,10]. The underlying mechanism is largely attributed to immersive distraction by heavily engaging the visual and auditory cortices. VR limits the brain’s cognitive capacity to process distressing environmental stimuli and nociceptive signals [9]. Consequently, this sensory gating dampens the activation of the sympathetic nervous system and the HPA axis, which theoretically translates to stabilized vital signs (heart rate, blood pressure) and reduced secretion of stress-related biomarkers such as salivary cortisol and alpha-amylase [7,8]. Furthermore, effectively mitigating preoperative anxiety has profound downstream clinical implications. Existing literature suggests that lower preoperative stress strongly correlates with smoother intraoperative anesthetic induction, decreased anesthetic requirements, and a reduction in postoperative pain perception and analgesic consumption [5,6]. However, existing literature in oral and maxillofacial surgery has predominantly focused on pediatric populations or minor procedures performed under local anesthesia. By investigating adult patients undergoing complex odontectomy under general anesthesia and using a robust combination of subjective psychometric tools and objective biochemical markers, this study addresses a significant gap in the current literature.

### Implications and Future Directions

The clinical implications of this trial are substantial. VR was specifically selected as the intervention modality because of its unique capacity to induce a profound sense of “presence,” effectively isolating the patient from the anxiety-inducing sights and sounds of the preoperative environment [10]. Compared to traditional nonpharmacological modalities such as audio therapy, 2D informational videos, or standard verbal pamphlets, immersive VR provides a significantly higher degree of sensory gating, making the psychological distraction far more potent [9,10]. Furthermore, when compared to standard pharmacological anxiolysis (eg, benzodiazepines), VR offers a safe, noninvasive, and easily reproducible alternative. It completely circumvents the inherent risks associated with sedative medications, such as respiratory depression, paradoxical reactions, and prolonged postoperative recovery times, factors that often contribute to patients’ underlying fear of general anesthesia itself [4]. If the hypothesized outcomes are achieved, immersive VR could fundamentally shift the paradigm of preoperative care in oral and maxillofacial surgery. This shift would not only enhance patient safety but also optimize hospital workflow by streamlining anesthetic induction and accelerating patient discharge. Future research should build upon these findings by evaluating the long-term impact of preoperative VR on postoperative variables, such as pain perception trajectories and wound healing, or by comparing different VR content to determine the most effective desensitization protocols.

